### Study setting and period

To estimate rIVE, the study population will include individuals vaccinated with the high-dose or standard influenza vaccine in mainland Portugal between the 2022/2023 and 2024/2025 seasons. When applicable, we will analyse each season (2022/2023, 2023/2024, 2024/2025) individually, starting after the implementation of each influenza vaccination campaign and ending nine months thereafter.

To estimate absolute IVE, the study population will include individuals for whom the high-dose influenza vaccine has been recommended in mainland Portugal for the 2024/2025 season. The study period will start after the implementation of the influenza vaccination campaign period and end nine months thereafter.

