### Outcome

The outcomes of interest are defined based on the primary cause of admission to a hospital, coded according to ICD-10, J11 (Influenza with pneumonia).

As a secondary outcome, we will also analyse cardiorespiratory hospitalisations as a primary cause of admission, with a secondary diagnosis of pneumonia, J12 (Viral pneumonia) and J18 (Pneumonia of unknown etiology).

Each of these outcomes will be analyzed separately. The outcome date will correspond to the hospitalisation date. Details on the ICD-10 codes are available in the Supplementary S1 Table.

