#### Censoring events.

All individuals will be followed from the start of the vaccination campaign until:

◦ Hospitalisation date (corresponding to the event date);◦ At the end of the study (nine months after the start of the vaccination campaign);◦ On the date of death (any cause)

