### Estimation of the vaccine effectiveness

A complete case analysis will be performed considering all variables in the final model to estimate adjusted-confounding IVE and stratified for each subgroup, individuals linving in LTCF and individuals living in the community (≥85 years)

We will use Cox proportional hazards regression models to estimate the hazard ratio (HR), considering the event the first hospitalisation due to influenza-like-illness and as exposure the vaccination status. The crude HR of vaccinated with the high-dose influenza vaccine vs vaccinated with the standard dose (rIVE) or unvaccinated (absolute IVE) will be estimated for each outcome of interest during the study period, without adjusting for other factors or covariates.

We will consider two sets of confounding factors. First, we will estimate partially adjusted HR, adjusting by age, sex and country region. Age will be modelled using a restricted cubic spline, with knots specified according to Harrell [12]. Second, a fully adjusted HR estimate will be produced by adjusting variables related to socioeconomic condition, comorbidities and health-seeking behaviour. IVE will be estimated as one minus the confounder-adjusted HR of vaccinated vs vaccinated with the standard dose (rIVE) or unvaccinated (absolute IVE) for each outcome of interest.

IVE = (1 - aHR) * 100

To estimate relative IVE, the time since vaccination will be modelled using a restricted cubic spline, with knots specified at zero and 15 days and then at the 40^th^ and 90^th^ percentile. To estimate absolute IVE for the time since vaccination (secondary objective), IVE will be estimated by comparing the hazard rate of the outcome in individuals vaccinated with the high-dose influenza vaccine for each class of the time since vaccination - 14–89 days, 90–179 days and 180–272 days (exposed group), in comparison with the outcome hazard rate in unvaccinated individuals (reference group).

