Despite its strengths, this study also has some limitations. We plan to use EHR, which does not aim to collect data for research purposes. Thus, this could lead to misclassification bias regarding vaccine status, outcomes, and confounding variables. For this reason, we might be unable to control for residual confounding since many relevant variables are not monitored or available in registries, and one should be aware that estimates can vary in the presence of confounding. Additionally, unvaccinated individuals will be the reference group when estimating absolute IVE. However, these individuals might differ from the vaccinated individuals due to their clinical profile or possible misclassification bias. Thus, we will use propensity score matching to account for this, assigning a probability of being vaccinated to each individual based on covariates. Considering that we will use EHRs, we might also be unable to correctly identify all individuals living in LTCF, as the report might vary geographically and temporally. Additionally, identifying these individuals might be associated with a differential bias, assuming that vaccinated individuals might be more likely to be reported as living in LTCF than unvaccinated. This situation is less likely to be problematic when estimating relative and absolute IVE in the community.

Another limitation is the potential outcome misclassification. In VE studies, it is extremely important to have sensible outcome definitions as the vaccines are designed to protect against influenza and related complications and studies use laboratory-confirmed outcomes. Using specific influenza ICD codes to identify severe influenza could underestimate severe influenza as the diagnosis is highly dependent on the testing strategy and, thus, on the codification attributed at discharge. On the other hand, including a broader range of ICD codes in the outcome definition could also underestimate IVE by including non-influenza-related outcomes. To balance this, we intend to use ICD codes that have been used for a long time in influenza surveillance and are highly sensitive. Finally, we intend to use discharge codes, as they are the final primary diagnosis of the hospitalisation. However, there are delays in hospital discharge and the codification of the hospitalisation event. In order to minimise this, the retrospective study will only use end-of-season data.

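### For the non-specific secondary outcome only, nine months of follow-up takes in weeks with little influenza, which attenuates IVE and leaves the 180–272 day class unable to show waning

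*Protocol article*

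**What the plan says.** **Window.** Under Study setting and period, each season's rIVE analysis is "starting after the implementation of each influenza vaccination campaign and ending nine months thereafter". For absolute IVE (2024/2025), "The study period will start after the implementation of the influenza vaccination campaign period and end nine months thereafter". Under Censoring events, "All individuals will be followed from the start of the vaccination campaign until" hospitalisation, death, or the administrative stop: "At the end of the study (nine months after the start of the vaccination campaign". No section restricts events or person-time to weeks when influenza circulates.

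**Outcomes.** Under Outcome, the main outcome is the primary cause of admission, "coded according to ICD-10, J11 (Influenza with pneumonia". In addition, "we will also analyse cardiorespiratory hospitalisations as a primary cause of admission, with a secondary diagnosis of pneumonia", with J12 and J18 named. The outcomes are analysed separately, and the code list is in a supplementary table that is not shown.

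**Time since vaccination.** This is a secondary objective, run only if numbers permit. For absolute IVE, the exposed classes are "14–89 days, 90–179 days and 180–272 days (exposed group", each compared with the unvaccinated. Neither Time since vaccination nor Estimation of the vaccine effectiveness says which outcome the classes apply to. For rIVE, time since vaccination is only a model covariate.

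**Acknowledged limit.** The Discussion grants that "including a broader range of ICD codes in the outcome definition could also underestimate IVE by including non-influenza-related outcomes". Its answer is to use sensitive codes that are long established in surveillance. Its reference to end-of-season data concerns delays in discharge and coding, not the period at risk.

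**The concern.** The secondary outcome mixes influenza admissions with pneumonia from other causes. An influenza vaccine can act only on the first kind, and that kind is concentrated in part of the year. Each further week with little influenza adds events on which the vaccine has no effect, so the hazard ratio moves away from its value in circulation weeks. The protocol recognises dilution by code choice but not dilution by calendar, and the second is the easier to remove.

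The same window bears on the time-since-vaccination classes. Follow-up starts at the campaign, so long time since vaccination is also late calendar time. For a non-specific outcome, a low IVE in the last class could mean that protection has faded or simply that influenza has gone.

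The abstract says the results will inform the Health Ministry's vaccine programme. An attenuated secondary estimate, or an apparent loss of protection after six months, could be misread there.

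**Working it through.** The protocol gives no event count, influenza share or expected effect for this outcome, so it has no figure to reproduce. The nine-month window, the class limits and the start of follow-up come from the protocol. Everything marked *assumed* does not.

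**1. Dilution.** If non-influenza admissions have hazard ratio 1, observed IVE = VE × f, where f is the influenza share of reference-group events. In circulation weeks f = s. Over nine months f = s × p, where p is the proportion of these admissions that fall in circulation weeks and no influenza occurs outside them. *Assumed:* VE 40%, s 15–35%, p 30–50%.

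- Circulation weeks: 0.40 × 0.15 = 6.0% to 0.40 × 0.35 = 14.0%.
- Nine months: 0.40 × 0.15 × 0.30 = 1.8% to 0.40 × 0.35 × 0.50 = 7.0%.

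**2. Cross-check with another set-up.** *Assumed:* non-influenza admissions constant over 39 weeks, influenza in w weeks only. With r = s/(1 − s), f = rw/(39 + rw). For s = 20% and w = 12, r = 0.25 and f = 3/42 = 0.0714. IVE is 0.40 × 0.20 = 8.0% in circulation weeks and 0.40 × 0.0714 = 2.9% over nine months. Over s = 5–30% and w = 8–20, the nine-month value keeps 21–60% of the in-season value.

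**3. Information.** Schoenfeld's formula (1:1, two-sided 0.05, 80% power) is 4 × (1.960 + 0.842)² / (ln HR)². In the example of step 2 it needs 4,516 events in circulation weeks and 37,364 over nine months, a factor of 8.3. Events available, in units of one week's background, rise only from 12 × 1.25 = 15 to 39 + 3 = 42, a factor of 2.8. The extra events cost more than they give.

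**4. The last class.** People vaccinated before the study start are excluded (Inclusion and exclusion criteria). Take campaign start as day 0 and nine months as day 273. Vaccination on day 0, 30, 60 or 90 then leaves 93, 64, 34 or 4 days in the 180–272 day class, so the whole class lies in about the last 93 days. For a campaign start between 1 September and 15 October (*assumed*), day 180 falls between 28 February and 13 April, and day 272 between 31 May and 14 July.

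Apparent IVE by class for the non-specific outcome, with true VE constant at 40% (no waning) and s = 20%, all *assumed*:

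| Circulation (study days) | Uptake spread over | 14–89 d | 90–179 d | 180–272 d |
|---|---|---|---|---|
| 70–154 | 45 days | 4.9% | 4.2% | 0.0% |
| 70–154 | 90 days | 6.1% | 2.4% | 0.0% |
| 90–174 | 45 days | 2.7% | 5.9% | 0.0% |
| 90–174 | 90 days | 5.0% | 4.0% | 0.0% |
| 100–212 | 45 days | 1.7% | 7.8% | 1.6% |
| 100–212 | 90 days | 4.1% | 6.6% | 1.2% |

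Over s = 10, 20 and 30%, the last class is 0.0–2.6% in every scenario, although protection never changes. The middle class is sometimes below and sometimes above the first, because the first includes pre-season weeks.

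**5. Residual confounding.** If the same background hazard ratio h applies in all weeks, off-season IVE is 1 − h: 20% at h = 0.8 and −10% at h = 1.1. In the example of step 2, h = 0.8 gives 1 − 0.8 × 0.92 = 26.4% in circulation weeks and 1 − 0.8 × 0.9714 = 22.3% over nine months. At h = 1.1 the values are −1.2% and −6.9%. The pull is towards 1 − h, which is zero only if h = 1.

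**6. J11.** An influenza-specific outcome has essentially no background events. Weeks without influenza add person-time but almost no events, so the dilution does not arise.

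**The case against.** **Scope.** The main outcome is J11, nothing is pooled with it, and the class analysis is a conditional secondary objective for absolute IVE only. This stands, and the point is confined accordingly.

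**Already disclosed.** The Discussion presents the code choice as a trade-off between sensitivity and specificity. That covers breadth of codes. It does not cover the length of the risk period, which the protocol fixes explicitly and which can be shortened without changing a code.

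**Same-date comparison.** Follow-up runs from campaign start, so a Cox model on that time axis compares people on the same date. This balances the season between exposure groups. It does not remove non-influenza events from the risk sets.

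**Invented inputs.** The influenza share, season length, true IVE and campaign date are all assumed. This stands for the sizes. The direction needs only that influenza's share of these admissions is lower off-season and that residual confounding is absent. The 11.2% rIVE in the Background is deliberately not diluted here: its endpoint is not defined in the article and may already include non-influenza admissions.

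**Narrow outcome.** The outcome may require a cardiorespiratory primary diagnosis together with a secondary pneumonia code. On either reading it admits pneumonia not caused by influenza.

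**Left to the full plan.** An off-season negative control is the kind of detail an article may omit, and asking for it is an improvement rather than the correction of an error. The nine-month window for every outcome, however, is stated here.

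**Conclusion.** The point holds for the secondary non-specific outcome. Following it for nine months attenuates IVE relative to circulation weeks: on the stated assumptions, from 6–14% to about 1.8–7.0%. The size rests on those assumptions, and the direction on the absence of residual confounding, which the Discussion admits may be present.

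If the classes are applied to this outcome, a low value at 180–272 days cannot be read as waning, given an autumn campaign start.

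A reader might infer more, but the document does not support it:

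- *The secondary outcome is bound to give a null result.* It does not follow; the illustrated values are small but not zero.
- *Both later classes will mimic waning.* Only the last class is reliably low; the 90–179 day class can move either way.
- *The time-since-vaccination objective as a whole, or the main result, is compromised.* The J11 analyses are largely unaffected.
- *Off-season IVE must be near zero.* That holds only without residual confounding.

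**What to change.** For the cardiorespiratory/pneumonia (J12/J18) outcome:

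- Make the main analysis the weeks of influenza circulation in each season, defined by a national-surveillance threshold fixed before the linked data are analysed.
- Report the remaining weeks of the same follow-up as a negative-control period. Adjusted IVE should be near zero there, and a clear departure would signal residual confounding.
- Report the time-since-vaccination classes only for J11, or only within circulation weeks, and say which outcome they apply to.

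J11 can keep nine months.

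The cost is fewer non-specific events in the main analysis, though by step 3 of the working the events dropped carry little information on the vaccine. A threshold must also be prespecified, and season dates must come from surveillance, which Data sources does not list and would need to add.

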### Vaccination status

To estimate rIVE, the vaccination status will be assessed retrospectively, and the time since vaccination will be estimated. The exposure of interest will be to receive the high-dose quadrivalent influenza vaccine, and the comparison group will be composed of those who received the standard-dose influenza vaccine.

To estimate absolute IVE, the vaccination status will be assessed as a time-changing variable according to the following classification:

◦ Unvaccinated: person-time of individuals without any quadrivalent influenza vaccine in the season.◦ Vaccinated: person-time of individuals who received a high-dose quadrivalent influenza vaccine dose during the study period. The completion status is achieved 14 days after administration of the dose.

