**Fig 1 pone.0314177.g001:**
[figure not shown]
Diagram of the two cohorts designed in this study. A – cohort of vaccinated individuals to measure relative influenza vaccine effectiveness, B – cohort of individuals eligible for the high-dose influenza vaccine to measure absolute influenza vaccine effectiveness. For the two cohorts, we will consider two subgroups: community-dwelling individuals aged ≥85 years and individuals living in LTCF and each cohort will begin every influenza season.

We will use a fixed cohort approach, defining the eligible population by their age at the start of the vaccination campaign(s) and living status. Table 1 describes the connection between the cohorts and the objectives.

**Table 1 pone.0314177.t001:** Summary of the study design with the different cohorts, objectives and exposed and unexposed groups.

Cohort	Subgroup	Objective	Exposed	Reference group
Vaccinated individuals (Fig 1, panel A)	Individuals living in LTCF	Estimate relative IVE of the high-dose quadrivalent influenza vaccine	Vaccinated with high-dose quadrivalent influenza vaccine	Vaccinated with standard influenza vaccine
	Individuals living in the community (≥85 years)			
Individuals eligible for influenza vaccination (Fig 1, panel B)	Individuals living in LTCF	Estimate absolute IVE of the high-dose quadrivalent influenza vaccine	Vaccinated with high-dose quadrivalent influenza vaccine	Unvaccinated individuals eligible for the high-dose quadrivalent influenza vaccine
	Individuals living in the community (≥85 years)			

IVE – influenza vaccine effectiveness; LTCF – long-term care facilities

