### Inclusion and exclusion criteria

The study population includes all registered individuals without contraindications for influenza vaccination residents in mainland Portugal. Only vaccinated individuals with the high-dose quadrivalent or standard influenza vaccine living in LTCF or community-dwelling individuals aged 85 or older will be included to estimate rIVE. Whereas, to estimate absolute IVE, only eligible individuals for the high-dose influenza vaccine living in LTCF or community-dwelling individuals aged 85 or older will be included.

We will exclude individuals with inconsistent or missing data on vaccination (e.g., any vaccination date unknown and any vaccine brand unknown), individuals who received any vaccine brand not approved by the European Medicines Agency (EMA), and individuals vaccinated before the study started.

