#### Time-changing characteristics (to estimate absolute IVE).

Vaccination status and time since vaccination will be assessed, and individuals will be classified into the same or updated vaccination status daily, generating a new record in the dataset for each new assessment. Person-time exposure between 0 and 13 days after vaccination will be excluded from the analysis.

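### The absolute-IVE reference state is defined by vaccine valency and no rule covers person-time after a standard-dose vaccine, so other vaccinees can enter the reference group and dilute absolute IVE

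*Protocol article*

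**What the plan says.** The section on vaccination status treats exposure for absolute IVE as time-changing and lists two states. The reference state is "Unvaccinated: person-time of individuals without any quadrivalent influenza vaccine in the season". The exposed state is "Vaccinated: person-time of individuals who received a high-dose quadrivalent influenza vaccine dose during the study period", counted as complete 14 days after the dose.

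Table 1 describes the reference group differently, as "Unvaccinated individuals eligible for the high-dose quadrivalent influenza vaccine", with no mention of valency.

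Entry to this cohort is by eligibility: "to estimate absolute IVE, only eligible individuals for the high-dose influenza vaccine living in LTCF or community-dwelling individuals aged 85 or older will be included". Besides inconsistent or missing vaccination data, the vaccine-related exclusions are "individuals who received any vaccine brand not approved by the European Medicines Agency (EMA), and individuals vaccinated before the study started". None of these removes a person who receives an approved standard vaccine during the season.

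Under time-changing characteristics, "individuals will be classified into the same or updated vaccination status daily", and only days 0 to 13 after vaccination are taken out. Under censoring events, follow-up ends at hospitalisation, at nine months, or at death.

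**The concern.** Absolute IVE is meant to compare high-dose recipients with people who have had no influenza vaccine. The relative-IVE analysis takes standard-vaccine recipients from the same two subgroups (long-term care residents and community-dwelling people aged 85 or older), and its seasons include 2024/2025, the only absolute-IVE season. Some people who are eligible for high dose, and so belong to the absolute-IVE cohort, should therefore be expected to receive another product.

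The text does not handle these people properly. The reference state turns on whether the product was quadrivalent, not on whether the person was vaccinated, and no rule says where person-time goes after a standard-dose quadrivalent vaccine. Two analysts working from the article could build different reference groups. If partly protected people end up in the reference group, its hazard falls and absolute IVE is underestimated. Propensity score matching on baseline covariates would not repair a misclassified reference group.

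**Working it through.** **Step 1: trace each kind of person through the stated rules (absolute IVE).**

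| Vaccine received in the season | Reference state? | Exposed state? | Excluded or censored? |
|---|---|---|---|
| None | Yes | No | No |
| High-dose quadrivalent | Before the dose | From day 14 | Days 0–13 removed |
| Standard-dose quadrivalent | Before the dose; not after it, by the words used | No | Follow-up continues; at most days 0–13 removed |
| Any non-quadrivalent product | Yes by definition, also after the dose | No | Follow-up continues; at most days 0–13 removed |

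The last row contradicts Table 1, where the reference group is simply unvaccinated. The third row is a gap: the person remains at risk in no defined state. Under the daily rule of keeping the same or an updated status, an analyst with no state to move that person to could leave them as unvaccinated.

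**Step 2: size of the dilution (illustration only).** The article states no expected absolute IVE, event count or sample size, so there is no figure of its own to reproduce. The inputs are:

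- Relative IVE of high dose against standard dose: 11.2%, from the Background section.
- True high-dose absolute IVE: 40% (assumption).
- s, the share of reference person-time that comes from recipients of another influenza vaccine: 10%, 30%, 50% (assumption).

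The formula also assumes that s is constant over follow-up and that these recipients would have had the same hazard as the truly unvaccinated without their vaccine.

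Hazard ratio of the other vaccine against no vaccine = 0.60 / (1 − 0.112) = 0.60 / 0.888 = 0.676, so its own effectiveness is v = 0.324.

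Observed absolute IVE = 1 − 0.60 / (1 − s × 0.324)

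- s = 10%: 1 − 0.60 / 0.968 = 38.0%
- s = 30%: 1 − 0.60 / 0.903 = 33.5%
- s = 50%: 1 − 0.60 / 0.838 = 28.4%

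**Step 3: sensitivity to the assumed effectiveness.** Now fix v, the effectiveness of the other vaccine, and set the high-dose hazard ratio to 0.888 × (1 − v). Observed absolute IVE is 1 − 0.888 × (1 − v) / (1 − s × v):

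| v | s = 0 (clean) | s = 10% | s = 30% | s = 50% |
|---|---|---|---|---|
| 20% | 29.0% | 27.5% | 24.4% | 21.1% |
| 30% | 37.8% | 35.9% | 31.7% | 26.9% |
| 40% | 46.7% | 44.5% | 39.5% | 33.4% |
| 50% | 55.6% | 53.3% | 47.8% | 40.8% |

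The loss is 1.5 to 2.3 percentage points at s = 10%, 4.6 to 7.8 at s = 30% and 7.9 to 14.8 at s = 50%. In the limit s = 100% the result is 11.2% for every v: absolute IVE has become relative IVE.

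**The case against.** The strongest reply has four parts.

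- **Standard-dose quadrivalent recipients are not counted as unvaccinated.** A reader might infer that the plan puts all standard-dose recipients in the reference group. It does not. The reference state requires no quadrivalent vaccine of any kind, so a standard-dose quadrivalent recipient drops out of it at the dose. Person-time in neither state dilutes nothing. Dilution by this route needs a further step, namely an analyst who carries the last status forward. This part stands: these people are unclassified, not expressly misclassified.
- **The contaminated share may be small or nil.** The article does not say that non-quadrivalent vaccines were given to these groups in 2024/2025, nor how many eligible people received another product. This also stands, and it makes the figures above illustrations only. However, the standard vaccine is named without a valency throughout, so the text does not rule such products out.
- **Table 1 shows the intent.** Read with Table 1, the word quadrivalent may be loose drafting. That is plausible, but the operational definition is the one an analyst would program, and the two do not agree.
- **A journal article leaves detail to the full protocol or analysis plan.** That would answer a missing detail. Here the article itself states an exposure definition and a list of follow-up end points that do not fit its own Table 1.

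A reader might also take the words about the season to mean that only people never vaccinated all season form the reference group, which would condition on future vaccination and bias absolute IVE upward. The document does not support this as a separate claim. The same section calls status time-changing, the definition is of person-time, and status is updated daily, so the time before a later dose belongs to the reference state. The size of any such bias would also depend on when in the season events occur, which the article does not state.

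**Conclusion.** The point holds as a defect in a stated definition and in the follow-up rule. By the literal text, recipients of a non-quadrivalent influenza vaccine are unvaccinated, against Table 1; recipients of a standard-dose quadrivalent vaccine remain under follow-up in no state. If either group is counted in the reference and its vaccine protects, absolute IVE is biased toward zero.

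The direction rests on the other vaccine being protective. The size rests on a share that the document does not give: with an assumed true IVE of 40%, the loss would be 2.0, 6.5 or 11.6 percentage points (40 minus 38.0, 33.5 and 28.4) at shares of 10%, 30% or 50%, and nothing if the share is zero. It should be fixed, because it concerns the contrast that defines absolute IVE, but the text does not establish that a bias of any particular size will occur.

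**What to change.** Two sentences, both for the absolute-IVE analysis.

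1. Vaccination status: define unvaccinated as all person-time from campaign start until receipt of any influenza vaccine of that season, whatever its dose or valency, including the pre-dose time of people vaccinated later. This brings the definition into line with Table 1 and also settles how the time before a later dose is counted.
2. Censoring events: add the date of receipt of any influenza vaccine other than the high-dose vaccine as a censoring date, or move the person to a separate exposure state on that date.

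The cost is small. The national vaccination registry already supplies influenza vaccination dates and brands, and the article says that no data had been accessed at submission, so the rule can be set in advance. The downside is that person-time after a standard dose does not contribute to the absolute-IVE contrast.
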